#### Secondary outcomes

Secondary outcomes are motivation to use the program, expectations for the intervention and engagement into the program. These outcomes are measured with tools incorporated into the program and self-report questionnaires at assessment time points.

Motivation is measured by a three item questionnaire created by the authors of this study. Expectations are measured as the difference of two 10-point Likert scale questions: 1) *How do you feel today before starting the intervention BADI?* 2) *How do expect to feel after using the intervention BADI for one month?* Participants are also asked to indicate how often they are planning to use the intervention in the upcoming month and the reasons for choosing this intervention. Engagement is measured by the number of exercises completed by the participant.

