### Aims of the study

There are two aims of this RCT: 1) to evaluate the effectiveness of an internet-based modular intervention for adjustment disorder (BADI); 2) to examine correlations between effectiveness, motivation, expectations, drop-out and adherence.

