#### Primary outcomes

The main outcome measures are psychological well-being and severity of Adjustment disorder symptoms. Level of adjustment disorder symptom severity is evaluated with Adjustment disorder new model (ADNM-20) [28] questionnaire. This questionnaire is constructed of a stressors list and evaluation of symptoms. The list is composed of seven of acute events (e.g. divorce, moving) and nine chronic stressors (e.g. conflict with neighbours, serious illness). Participants are instructed to indicate all severe events from the list that they had experienced in the last 2 years and that caused significant level of stress. There is also a blank item for participants to fill in other significant stressors. Psychometric properties of the Lithuanian version of the ADNM-20 questionnaire are acceptable [7].

The WHO-5 Well-being Index (WHO-5) [29] is a short self-report measure for well- being assessment. Participants are asked to rate how each of the 5 statements applies to them when considering the last 2 weeks. Each item is scored from 5 (all of the time) to 0 (none of the time). The raw score therefore ranges from 0 (absence of well-being) to 25 (highest well-being). Participants who score > 16 on ADNM and < 50 on WHO-5 are included into the study.

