#### Statistical analysis

All data will be analysed using Statistical Package for the Social Sciences (SPSS) version 20. Differences between groups at baseline will be investigated using *χ*^2^ tests of independence for categorical measures and t-tests for continuous measures. Intent-to-treat approach will be applied to the primary efficacy analysis from T1 to T2. Per-protocol and completer analysis will be performed as secondary. Mixed ANOVA with post hoc tests will be used to test effect of time and interactions between groups in time. Cohens’ *d* will be calculated for estimation of within and between group effect sizes.

Drop-out is considered if a participant uses the program at least once but does not complete self-report at T2. Engagement in this study is defined by the number of exercises completed by participant, i.e., the more exercises a participant completes the more engaged participant is considered.

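### Correlating the expectation difference score with effectiveness, with no adjustment stated for baseline state, biases that one association within Aim 2

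*Protocol article*

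**What the plan says.** Under Secondary outcomes, "Expectations are measured as the difference of two 10-point Likert scale questions". The two items are "How do you feel today before starting the intervention BADI" (below, F) and "How do expect to feel after using the intervention BADI for one month" (below, E). The direction of subtraction is not stated.

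Aims of the study gives as the second aim "to examine correlations between effectiveness, motivation, expectations, drop-out and adherence", and the article's Discussion repeats the list.

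No per-participant effectiveness variable is defined. The nearest statements are "The main outcome measures are psychological well-being and severity of Adjustment disorder symptoms" (Primary outcomes) and "Intent-to-treat approach will be applied to the primary efficacy analysis from T1 to T2" (Statistical analysis). The only model named is for the group comparison: "Mixed ANOVA with post hoc tests will be used to test effect of time and interactions between groups in time". For the expectation–effectiveness association, the article states neither an adjustment for baseline state nor separate use of the two items.

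**The concern.** A participant who feels bad on the day of the first assessment scores low on F. That enlarges E − F whatever the participant expects. The same low state at T1 tends to be followed by a larger rise by T2, through regression to the mean. Expectation score and improvement are thus linked through the state at T1, and a plain correlation cannot separate this link from an effect of expectancy. The trial could then report a baseline artefact as evidence that expectations drive benefit, under an aim it names explicitly.

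**Working it through.** The protocol gives no figure for this association, so there is none to reproduce. Only the sample size is used from it.

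**Inputs from the protocol.** 190 randomised, 1:1, 30 % attrition (Sample size; Randomization). One arm: 190 / 2 × 0.7 = 66.5, taken as 66. Both arms: 190 × 0.7 = 133.

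**Assumed inputs, not in the protocol.** Y0 and Y1 are the outcome at T1 and T2, scored so that higher is better.
- r = corr(F, Y0): 0.3 to 0.7
- ρ = corr(Y0, Y1): 0.3 to 0.7
- c = corr(E, F): 0 to 0.5
- Equal SDs within each pair of measures.
- Null model: E relates to the outcome only through F, and F relates to Y1 only through Y0.

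**Step 1: effectiveness as improvement.** With unit SDs,

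cov(E − F, Y1 − Y0) = crρ − cr − rρ + r = r(1 − ρ)(1 − c)

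The variances are 2(1 − c) and 2(1 − ρ), so

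corr = (r / 2) × √[(1 − ρ)(1 − c)]

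- Smallest (r 0.3, ρ 0.7, c 0.5): 0.15 × √0.15 = 0.058
- Middle (0.5, 0.5, 0.3): 0.25 × √0.35 = 0.148
- Largest (0.7, 0.3, 0): 0.35 × √0.70 = 0.293

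**Step 2: effectiveness as the raw T2 score.** corr(E − F, Y1) = −rρ√[(1 − c)/2]. The middle case gives −0.25 × √0.35 = −0.148. In the five simulated settings of Step 4 without truncation it was −0.08 to −0.21. The bias remains and its sign reverses.

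**Step 3: false-positive rate for Step 1.** By Fisher z, with m = atanh(corr) × √(n − 3), the rejection rate is 1 − Φ(1.96 − m) + Φ(−1.96 − m). For the middle case at n = 66, m = 0.149 × √63 = 1.18, which gives 22 %.

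| Case | Null correlation | n = 66 | n = 133 |
|---|---|---|---|
| Smallest | 0.058 | 7 % | 10 % |
| Middle | 0.148 | 22 % | 40 % |
| Largest | 0.293 | 67 % | 93 % |

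**Step 4: selection at entry.** "Participants who score > 16 on ADNM and < 50 on WHO-5 are included into the study", which narrows the baseline range. To mimic this, Y0 was cut off at +0.3 SD (assumed), with F and E rounded to 1–10, in 3000 simulated trials per setting at n = 66:

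| r, ρ, c | Mean correlation, no cut | Rejection, no cut | Mean correlation, cut | Rejection, cut |
|---|---|---|---|---|
| 0.3, 0.5, 0.3 | 0.088 | 10.7 % | 0.036 | 5.5 % |
| 0.5, 0.5, 0.3 | 0.149 | 22.7 % | 0.067 | 8.0 % |
| 0.5, 0.5, 0 | 0.167 | 27.2 % | 0.083 | 9.6 % |
| 0.7, 0.5, 0.3 | 0.204 | 38.1 % | 0.097 | 12.2 % |
| 0.7, 0.3, 0 | 0.293 | 68.4 % | 0.146 | 22.8 % |

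With the cut and n = 133, rejection was 7.9 % to 40.5 %. The cut roughly halves the artefact but does not remove it. With r = 0 there is no artefact (mean correlation −0.002, rejection 5.4 %).

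**Step 5: the alternative.** Regressing Y1 on E, F and Y0 as separate terms and testing the coefficient of E gave rejection rates of 4.0 % to 5.4 % in every null setting, cut or not.

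**The case against.** The strongest reply is that the criticised analysis is partly inferred. Effectiveness is not defined per participant, no method is given for Aim 2, and covariates for a secondary association are commonly left to an analysis plan that is not shown. An adjusted correlation would be compatible with the aim as worded. This stands as a limit on certainty. But the score and the intention to correlate it are fixed in the article, and taken literally they give a biased answer under either reading of effectiveness.

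Also correct: the difference score is not itself an error. Since b₂E + b₁F = b₂(E − F) + (b₁ + b₂)F, its coefficient equals that of E once F and the T1 score are in the model. What is needed is the adjustment.

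Three stronger readings are tempting, and the document does not support them.

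- *The correlation is positive by construction.* The two differences share no term: F is a single rating for today, whereas WHO-5 covers two weeks. The link is indirect, and its sign depends on an unstated direction of subtraction and an undefined effectiveness variable.
- *Aim 2 as a whole is compromised.* Only the expectation–effectiveness pair is. What the abstract says about expectancies concerns engagement, a count of completed exercises, to which this coupling does not apply.
- *The motivation and engagement associations need the same repair.* No such coupling has been shown for them.

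Finally, the size rests on assumptions. The high rates belong to an unselected baseline and, at the top, to uncorrelated E and F. If F also predicts T2 directly (assumed correlation 0.35 with T2, 0.5 with T1; ρ 0.5, c 0.3), the null correlation is 0.15 × √0.7 / (2 × √0.5) = 0.09, with rejection about 11 % at n = 66.

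**Conclusion.** The point holds for one association. An unadjusted correlation of the expectation score with effectiveness is biased by the state at T1 even when expectations have no influence. For expected-minus-today against improvement, the null correlation is about 0.06 to 0.29 if the assumed correlations describe the enrolled sample. It is about 0.04 to 0.15 if they describe an unselected population that the entry criteria then truncate. In the mildest truncated setting the practical effect is negligible. In the others the nominal 5 % level is not kept.

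These figures rest on the assumed r, ρ and c, equal SDs and the assumed cut-off. For improvement, the artefact disappears only if the today rating is unrelated to the T1 outcome, or if ρ or c is close to 1. The primary randomised comparison is untouched. This is worth correcting, but it does not threaten the trial's main result.

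**What to change.** State for this association only: the T2 score (WHO-5 and ADNM-20 in separate models) is regressed on its T1 score, the today rating and the expected rating as separate terms, and the expectancy effect is the coefficient of the expected rating. Keeping the difference score and adjusting it for the today rating and the T1 score is equivalent. This also makes a separate definition of per-participant effectiveness unnecessary here, because with the T1 score in the model, T2 and T2 − T1 give the same coefficient. The coefficient remains an association and should be reported as such.

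The cost is one sentence in the analysis section. Both ratings and the T1 and T2 scores are already collected, and the planned software can fit the model. The motivation, engagement and drop-out correlations need no change on this account.

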### Analysis

#### Sample size

To achieve an improvement of 10 in mean scores of WHO-5 Well-being index we calculated about 73 participants per study arm to achieve 80 % power at α = .05. Factoring in the 30 % attrition rate, we seek to randomize a total of 190 participants.

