#### Randomization

The randomization process is continuous in a way that the participant is instantly allocated to the intervention or waiting-list control group within 24 h of completing the initial assessment. Randomization is conducted by study team member using an online true random number service www.random.org. Participants are randomized in 1:1 ratio to study groups. No stratification is applied.

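### Randomising 190 participants does not leave 73 per arm after 30 % attrition; on the plan's own figures power is about 76 %, not 80 %

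*Protocol article*

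**What the plan says.** The Sample size section of the protocol article fixes four quantities:

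- the target effect: "To achieve an improvement of 10 in mean scores of WHO-5 Well-being index";
- the number required: "we calculated about 73 participants per study arm", in order "to achieve 80 % power at α = .05";
- the allowance for losses: "Factoring in the 30 % attrition rate";
- the recruitment target: "attrition rate, we seek to randomize a total of 190 participants".

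The Randomization section adds the allocation: "Participants are randomized in 1:1 ratio to study groups". The section gives no standard deviation, sidedness or test, and nothing elsewhere in the article offers another basis for 190. The Statistical analysis section plans an intention-to-treat primary analysis from T1 to T2 by mixed ANOVA.

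**The concern.** If 73 per arm is the number needed once losses have occurred, the randomised total must still contain 146 participants with outcome data after 30 % are gone. A total of 190 does not. The stated requirement, attrition and total therefore cannot all be right, and 80 % power does not follow from them.

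This paragraph is the trial's only justification of its size. It covers one endpoint, the WHO-5, which is one of the two primary outcomes. Attrition is not a side issue here either: the intervention is self-directed and online, and drop-out is part of the second study aim. A reader who takes the paragraph at its word will believe that the trial keeps 80 % power at 30 % loss.

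**Working it through.** **Inputs.** From Sample size: 73 per arm, 80 % power, α = 0.05, a 10-point difference, 30 % attrition, 190 in total. From Randomization: 1:1. Assumed, because not stated: a two-sided two-sample t-test and equal loss in both arms. The one-sided case is also shown.

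**1. Reproducing the stated total.**

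- Required with outcome data: 2 × 73 = 146.
- Multiplying: 146 × (1 + 0.30) = 189.8, which rounds to 190. This is the stated figure.
- Dividing: 146 / (1 − 0.30) = 208.6, so 209. Per arm, 73 / 0.7 = 104.3, so 105 per arm and 210 in total.

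Only the multiplication returns 190. The article does not show its working, so this is an inference from the match.

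**2. What 190 delivers.**

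- After 30 % loss: 190 × 0.7 = 133, or 66.5 per arm.
- Shortfall: 146 − 133 = 13 participants.
- Highest attrition at which 146 remain: 1 − 146/190 = 23.2 %.

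None of this needs a standard deviation.

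**3. Effect on power.** Solving the two-sided t-test for 80 % power at 73 per arm gives a standardised difference d = 0.467, so the implied SD is 10 / 0.467 = 21.4. Holding d fixed:

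| Per arm with outcome data | Power, two-sided | Power, one-sided |
|---|---|---|
| 73 | 80.0 % | 80.0 % |
| 67 | 76.5 % | 76.9 % |
| 66 | 75.9 % | 76.4 % |

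The one-sided column uses its own back-solved value, d = 0.414 (SD about 24.2). With 66 to 67 per arm, the difference detectable with 80 % power (two-sided) is 10.4 to 10.5 points instead of 10.0.

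**4. Allowing for the word *about*.** Reading the requirement as 70 to 75 per arm, division by 0.7 gives 140/0.7 = 200 to 150/0.7 = 214.3, so 200 to 215 in total. At every value in that range 190 is too small.

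**The case against.** The strongest reply leaves the arithmetic alone and disputes the power figure. There are four parts to it.

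- **The analysis is not a T2-only t-test.** The mixed ANOVA uses T1 as well. If 73 was sized on T2 scores alone, the group-by-time test at 66.5 per arm behaves like a change-score comparison. Its power would be about 62 % at an assumed T1–T2 correlation of 0.3, 76 % at 0.5, 80 % at 0.55 and 85 % at 0.6. Actual power could lie on either side of 80 %. This stands as a caution: the 76 % is conditional on the plan's implied inputs. It does not rescue the paragraph, which claims no such gain.
- **Loss might fall on one arm only.** The Statistical analysis section defines drop-out by use of the program, and waiting-list participants have no access before T2. With 30 % lost from the intervention arm alone (66 to 67 against 95), power is about 82.5 to 82.9 %. However, the sizing paragraph speaks of attrition in general, the match to 146 × 1.3 points to one common inflation, and the intervention arm would still fall below 73.
- **Intention to treat keeps everyone.** The plan itself inflates for attrition, so it treats 73 as the number left after losses. A missing T2 self-report does not carry full information.
- **The loss is small.** That is true: about four percentage points, with no bias in the estimate and no effect on the type I error. It bears on how much the error matters, not on whether the statement is correct.

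**Conclusion.** The concern holds. The requirement of 73 per arm, the 30 % allowance and the total of 190 contradict each other whatever the SD, sidedness or test. If the allowance applies to the whole randomised sample, the total is 19 to 20 participants too low (209 or 210 against 190), and 133 rather than 146 remain.

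The consequence for power is modest: about 76 % instead of 80 %, or a detectable difference of about 10.5 instead of 10 points. Those figures rest on equal loss in both arms, a two-sample t-test, and the SD of about 21.4 back-solved from the plan's own 73 per arm. The multiplication by 1.3 is a strong inference, and the conclusion does not depend on it.

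**What to change.** Rewrite the last sentence of the Sample size section so that its numbers agree. The least costly form keeps the target and corrects the claim: with 190 randomised (95 per arm), 30 % attrition leaves about 66 to 67 per arm and about 76 % power for a 10-point WHO-5 difference, while 80 % power is kept if attrition does not exceed 23 %. State the SD, sidedness and test on which the figures rest, since the 76 % is otherwise back-solved.

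This costs one corrected sentence and a slightly less favourable power statement; design, analysis and recruitment stay as they are. If the sponsor prefers to keep the claim of 80 % power at 30 % attrition, the target becomes 210 (105 per arm), which is 20 more participants.

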#### Statistical analysis

All data will be analysed using Statistical Package for the Social Sciences (SPSS) version 20. Differences between groups at baseline will be investigated using *χ*^2^ tests of independence for categorical measures and t-tests for continuous measures. Intent-to-treat approach will be applied to the primary efficacy analysis from T1 to T2. Per-protocol and completer analysis will be performed as secondary. Mixed ANOVA with post hoc tests will be used to test effect of time and interactions between groups in time. Cohens’ *d* will be calculated for estimation of within and between group effect sizes.

Drop-out is considered if a participant uses the program at least once but does not complete self-report at T2. Engagement in this study is defined by the number of exercises completed by participant, i.e., the more exercises a participant completes the more engaged participant is considered.

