Social support is another important part of effective coping with stress [27]. BADI relationships module includes partner encouragement exercise, assertive message and appreciation which enhance stress coping through open communication and social support [18, 21].

Exercises take from 5 to 15 min to complete. The participant may complete as many or as few modules as they choose. This enables a participant to personalize the intervention to his needs. The participants are instructed that they will have access to BADI for one month.

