### Study groups

#### Intervention BADI

Participants in the intervention BADI group have full access to the intervention modules for 30 days. Participants can freely select any of the BADI intervention exercises. Participants can complete as many or as little exercises as they need. Participants can do exercises in any order they prefer. There are no instructions to complete all exercises. Participants can choose to complete one or more exercises and do them repeatedly. Weekly remainder e-mails are sent once per week to participants. Participants are reminded that for stress management skills to improve they need to use the intervention as frequently as possible.

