#### Waiting-list control

Participants in the waiting-list control group are asked to continue with their everyday life and come back for a secondary assessment after 30 days, after completing the secondary assessment they receive access to the intervention for one month.

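### If the planned per-protocol set is defined by use, it filters the intervention arm alone: the protocol sets no amount of use and the waiting list has no access before T2.

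*Protocol article*

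**What the plan says.** The Statistical analysis section makes intention to treat primary: "Intent-to-treat approach will be applied to the primary efficacy analysis from T1 to T2". It then adds: "Per-protocol and completer analysis will be performed as secondary". The per-protocol set is not described further, but it is named separately from the completer analysis.

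On use, the BADI intervention section says: "The participant may complete as many or as few modules as they choose". The Intervention BADI section says "Participants can complete as many or as little exercises as they need" and "There are no instructions to complete all exercises". The weekly e-mails remind participants that "they need to use the intervention as frequently as possible", without naming an amount. Engagement is a count with no threshold: "the more exercises a participant completes the more engaged participant is considered".

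For the control arm, the Waiting-list control section says that "after completing the secondary assessment they receive access to the intervention for one month".

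**The concern.** A per-protocol analysis presupposes a standard that participants can meet or miss. On use, this protocol has none: one exercise and fifty are equally in line with the instructions. A use-based set would therefore need a cut-off that the protocol does not supply. Because the waiting list has no use between T1 and T2, that cut-off could remove people from one arm only.

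The result would be a comparison of participants who chose to use the program with controls who were not sorted in that way. The second aim examines how motivation, expectations and adherence relate to effectiveness, so the trial itself treats it as plausible that users differ from non-users in ways that bear on outcome. A secondary result of this kind could suggest a benefit where there is none, or hide one, and a cut-off chosen after the data are seen would make it hard to interpret.

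**Working it through.** **Reading the sections together**

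1. Required use in the intervention arm: none (BADI intervention; Intervention BADI). Frequent use is encouraged, with no threshold.
2. Possible use in the waiting list before T2: none (Waiting-list control).
3. Per-protocol and completer analyses are listed as two things (Statistical analysis). Having T2 data alone therefore does not appear to define the per-protocol set, and use is the natural remaining criterion. This is an inference; the article does not say so.
4. From 1 to 3, a use-based set selects on behaviour after randomisation in one arm only. Controls are unselected on use, though they are still selected on returning at T2.

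**Implied SD**

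The Sample size section gives a 10-point WHO-5 difference, about 73 per arm, 80% power and α = .05. It states neither an SD nor sidedness. Taking a two-sided test:

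SD = 10 × √(73/2) / (1.960 + 0.842) = 21.6.

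Conversely, SD 21.5 gives n = 2 × (2.802 × 21.5 / 10)² = 72.6, which rounds up to the stated 73. I use 21.5. It is an implied value (a one-sided test would imply about 24.3), and it applies on the scale of the 10-point target.

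**Illustration of the bias with no true effect**

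Assume that the per-protocol set is the top share p of intervention participants on a normally distributed use score, that this score correlates r with the outcome, and that controls are not selected on use. Then

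bias = r × λ × SD, with c = Φ⁻¹(1 − p) and λ = φ(c)/p.

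For the upper half, λ = 0.798:
- r = 0.1: 0.1 × 0.798 × 21.5 = 1.7 points
- r = 0.2: 0.2 × 0.798 × 21.5 = 3.4 points
- r = 0.3: 0.3 × 0.798 × 21.5 = 5.1 points

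For a looser rule at r = 0.3:
- 80% kept, λ = 0.350: 0.3 × 0.350 × 21.5 = 2.3 points
- 90% kept, λ = 0.195: 0.3 × 0.195 × 21.5 = 1.3 points

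For the chance of a false two-sided rejection, take 190 × 0.70 / 2 = 66.5 assessed per arm. In SD units the standard error is √(v/(66.5p) + 1/66.5), with v = 1 − r²λ(λ − c). With the upper half kept, rejection is 6.6%, 11.8% and 21.0% for r = 0.1, 0.2 and 0.3. At r = 0.3 it falls to 8.9% with 80% kept and 6.3% with 90% kept.

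A negative r reverses the sign of every bias figure.

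**The alternative under the same conditions**

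With no access on the waiting list before T2, the complier-average effect without covariates is

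intention-to-treat difference / proportion of the intervention arm with at least one completed exercise.

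If the true difference is zero, the numerator has expectation zero whatever the link between use and prognosis, so this selection creates no spurious effect. The price is precision: treating the proportion as known, 80% users would make the standard error 1/0.80 = 1.25 times that of the intention-to-treat difference.

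**The case against.** The strongest reply is that the article is a condensed protocol, and that defining a per-protocol set is commonly left to an analysis plan that is not shown. That stands as far as it goes: the missing definition is not the point. The point is that the article declares any amount of use acceptable and gives one arm no access, so an analysis plan cannot derive a use standard from it, and any standard that it invents acts on one arm only.

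Several further objections stand and limit the claim:

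- A reader might infer that every per-protocol set here must rest on a use cut-off. The documents do not support that. Eligibility, exclusion criteria and the 30-day timing of T2 apply to both arms and could define the set.
- A use threshold of sorts does exist: the drop-out definition refers to having used the program at least once. It too cannot apply to the waiting list before T2.
- A reader might take 5.1 points, about half the 10-point target, as the expected bias. It is one scenario. The SD is not stated, keeping half of users is arbitrary, and the implied SD may not be the right one for a time-by-group analysis. The sign is also assumed: participants do what they feel they need, so heavier use may mark worse adjustment.
- A reader might infer that the trial will read its engagement correlations as a dose effect. The stated aim is only to examine correlations; no such claim is made.
- The complier-average effect needs its own assumption, that allocation does nothing for those who complete no exercise. Participants are unblinded, outcomes are self-reported, and the reminder e-mails are described for the intervention group, so this is open to question. Nor does the method solve missing T2 data.

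**Conclusion.** The concern holds in conditional form. If the per-protocol set is defined by use, it is a one-arm selection on behaviour after randomisation, and the comparison is no longer a randomised one. That follows from the protocol's own statements on free use and delayed access. That the set will be defined by use is the natural reading, not a stated fact.

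The size cannot be determined from the documents. Under the assumptions above, a spurious difference of about 1.7 to 5.1 WHO-5 points is possible with half of users kept, and about 1.3 to 2.3 points at r = 0.3 with 80 to 90% kept. Either could run against BADI. A reader might conclude that the trial's main result is at risk. It is not, because the primary efficacy analysis is by intention to treat and this one is secondary. The change is worth making but is not critical.

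**What to change.** Replace any use-based per-protocol comparison with a complier-average causal effect: randomisation as instrument, at least one completed exercise as compliance, T1 score as covariate, and the same handling of missing T2 data as in the intention-to-treat analysis. Report it as a secondary sensitivity estimate and state the assumption about participants who complete no exercise, with the reasons to doubt it.

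If a per-protocol set is kept, fix it before the data are seen. Either build it from criteria that apply to both arms, such as eligibility and T2 timing, or label the comparison exploratory and non-randomised.

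The cost is one two-stage regression on data that the trial already collects, since exercise counts are the engagement measure. The downsides are a wider confidence interval and reliance on the assumption just named.

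### The drop-out definition can apply only to BADI-arm participants who started the program, and because it requires a missing T2 it cannot be related to observed effectiveness as Aim 2 intends

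*Protocol article*

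**What the plan says.** All references are to the Protocol article.

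- **Statistical analysis** gives the only definition of drop-out: "Drop-out is considered if a participant uses the program at least once but does not complete self-report at T2". The same paragraph defines engagement as the count of completed exercises. On efficacy it says: "Intent-to-treat approach will be applied to the primary efficacy analysis from T1 to T2".
- **Waiting-list control** says of that group's access: "after completing the secondary assessment they receive access to the intervention for one month".
- **Intervention BADI** sets no minimum use: "Participants can complete as many or as little exercises as they need".
- **Aims of the study** gives the second aim: "to examine correlations between effectiveness, motivation, expectations, drop-out and adherence". The Discussion repeats it.
- **Sample size** allows for 30 % attrition and seeks 190 participants in total. **Randomization** says: "Participants are randomized in 1:1 ratio to study groups". The 30 % is not tied to the drop-out definition.

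**The concern.** The definition has two conditions, and each causes a different problem.

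The first condition, having used the program, limits drop-out to people who had access before T2 and took it up. That removes every waiting-list participant and every BADI participant who never opened the program. If the resulting count were read as trial attrition, it would be too low and would show losses in one arm only. It would then be no basis for judging attrition bias or the 30 % planning figure.

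The second condition, not completing T2, makes drop-out incompatible with having an observed outcome. Aim 2 lists drop-out and effectiveness among the quantities to be correlated, and effectiveness is measured from T1 to T2. No participant can be a drop-out and also have an observed change.

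**Working it through.** **Notation.** For each randomised participant let U = 1 if the program was used before T2, R = 1 if T2 was completed, and D = 1 if the participant is a drop-out. The stated rule is D = U × (1 − R). I take the 30-day assessment in the waiting-list section to be T2; the flow chart is not shown.

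**Step 1: who can be a drop-out**

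| Participant | U | R | D |
|---|---|---|---|
| Waiting list, T2 missing | 0 (no access yet) | 0 | 0 |
| Waiting list, T2 completed | 0 (access comes afterwards) | 1 | 0 |
| BADI, never used, T2 missing | 0 | 0 | 0 |
| BADI, used, T2 missing | 1 | 0 | **1** |
| BADI, T2 completed | 0 or 1 | 1 | 0 |

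Only one row gives D = 1. Control-arm drop-out is zero by construction.

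**Step 2: the plan's own total.** From 73 per arm and 30 % attrition: 73 × 1.30 = 94.9, taken as 95 per arm, and 2 × 95 = 190. This reproduces the stated total. It is used here only for the arm size; whether it is the right way to allow for attrition is a separate question.

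**Step 3: how many losses the rule would count.** Assume 30 % loss to T2 in each arm. The article gives no split by arm.

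- Losses in total: 0.30 × 190 = 57, or 28.5 per arm.
- Waiting-list losses counted: 0 of 28.5.
- BADI losses counted: 28.5 × (1 − v), where v is the share of BADI-arm losses who never used the program.

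The article gives no value for v, so a range is shown.

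| v (assumed) | Counted | Share of 190 |
|---|---|---|
| 0 | 28.5 | 15.0 % |
| 0.10 | 25.65 | 13.5 % |
| 0.25 | 21.4 | 11.2 % |
| 0.50 | 14.25 | 7.5 % |
| 0.75 | 7.1 | 3.8 % |

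With equal loss in the two arms, at least half of all losses fall outside the definition whatever the loss rate.

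**Step 4: drop-out against observed change.** An observed T1 to T2 change requires R = 1. Then D = U × 0 = 0 for everyone, so the variance of D is 0 and r = cov / (SD × SD) = 0/0, which is undefined. The cause is the factor (1 − R), not U. Redefining drop-out as any missing T2, D = 1 − R, again gives D = 0 whenever R = 1, so widening the definition does not help.

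**Step 5: drop-out against imputed change.** As an illustration, one BADI arm of 95 was simulated with assumed values: mean change 10, SD 21.5, 80 % starters, 30 % missing T2, all generated independently. Carrying the baseline forward sets change to 0 for everyone without T2. The coefficient between drop-out and change was then about −0.25, although the data were generated with no association. That value came from the imputed zeros.

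**Step 6: what remains computable.** Baseline motivation and expectations do not depend on R, and D varies in the BADI arm, so those associations can be calculated there. So can drop-out against the number of exercises.

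**The case against.** The strongest reply is that the definition describes treatment drop-out among starters and was never meant to measure trial attrition. It stands beside the definition of engagement, and the second aim groups drop-out with motivation, expectations and adherence. On that reading, leaving out people who never had or never opened the program is intended. Never-users are not lost to the analysis either, since they score zero on engagement. Much of this stands. A reader might infer that the trial will report attrition in one arm only and understate the 30 %. The article does not support that: nothing in it makes this label govern participant flow, the sample size allowance, missing-data handling or any analysis set.

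The starter reading does not rescue the definition altogether. A participant who stops after one exercise but returns T2 is not a drop-out, while a heavy user who misses T2 is. That is an odd measure of treatment discontinuation.

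A reader might also infer that Aim 2 as a whole fails, or that the drop-out-by-effectiveness coefficient cannot be computed at all. Neither follows. The aim lists five quantities without committing to every pair, several drop-out pairs remain computable, and intent-to-treat with filled-in T2 values would return a number. What stands is narrower: that number would not come from observed outcomes.

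**Conclusion.** The concern holds in limited form, at moderate severity.

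- **As an attrition measure** the definition is unusable: it can fit only BADI-arm starters. At most 28.5 of 57 losses would count, given 95 per arm and an assumed equal 30 % loss, and fewer if some BADI-arm losses never used the program. These figures show the gap between the label and loss to T2. They do not predict what the trial will report.
- **For Aim 2**, the number of drop-outs with an observed effectiveness value is exactly 0. This follows from the definition and needs no assumption about loss rates.
- **Not affected directly:** the primary intent-to-treat comparison, and drop-out against baseline motivation or expectations in the BADI arm.

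A reader might take this as a defect that must be repaired before the main result can be trusted. The article does not support that, because no part of the primary analysis is defined through the drop-out label.

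**What to change.** Replace the single definition with two.

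(a) **Study attrition:** any randomised participant without T2, reported by arm and including never-users. Use this for participant flow, for assessing missing data and for comparison with the 30 %.

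(b) **Treatment discontinuation or non-usage:** defined in the BADI arm from program records and independently of T2, for example zero exercises completed, or no exercise after a week fixed in advance. Use this, or the number of exercises, for the association with effectiveness.

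Any T2-based drop-out variable should be related only to baseline predictors or usage. Definition (a) alone would not make the association with effectiveness estimable (Step 4), so (b) is needed as well.

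The cost is two sentences, settled before the Aim 2 analysis. T2 completion and exercise counts are already collected. A rule based on a cut-off week would also need dated usage records, which the article does not mention.
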